## 4. Conclusions

The incorrect use of child car seats is a common problem that may be reduced through enhanced instructional material. This process evaluation of our randomised controlled trial of additional instructional material for installation and securing the child will systematically evaluate intervention delivery and external factors that may impact the effectiveness of the intervention, grounded on a behavioural change theoretical framework. It will provide enhanced understanding of the mechanisms through which the intervention works or not, aspects of the implementation process key to the success or otherwise of the intervention, and insight into how external factors influence the success or otherwise of the intervention.

## Figures and Tables

**Figure 1 ijerph-17-04508-f001:**
[figure not shown]
Logic model describing the hypothesised relationship between the intervention being tested and the primary trial outcome, the correct use of the restraint at six months post-purchase.

**Table 1 ijerph-17-04508-t001:** Process measures.

Component/Logic Model Link	Measures	Method	Data Type
Fidelity, Dose Delivered/Output Activities	A3 instructions & swing tags received, QR codes & web links work	Assumed 100%	N/A
Dose received/Output Participation	A3 instruction sheet participation score (aware received A3 instructions, read instructions, retained instructions, stored correctly, re-used instructions); swing tag participation score (aware received swing tags, used swing tags, swing tags attached to restraint, swing tags used frequently); video participation score (accessed video, used video, re-accessed video)	Survey questions	Continuous
Proximal Outcome	Comprehends and recalls key tasks	Survey question	Categorical
Medial Outcome	Did the participant continue to check key components of correct use?	Survey question	Categorical
Distal (Primary) Outcome	Was the restraint used correctly at six- month visit?	Home visit check	Categorical
External Factors	Health literacy level, prior experience with car seats, access to correct use information from other sources, use of a restraint fitter, confidence/attitude	Single item health literacy, survey questions	Health literacy continuous/all others categorical

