
### 2.1. The Intervention and Randomised Controlled Trial

The intervention materials consist of an A3 size instruction sheet, a set of four swing tags designed to be fixed to the restraint and an online video demonstrating the overall instructions and use process, as well as separate video snippets relevant to key tasks. The video is accessible via QR codes printed on the A3 instruction sheet and on the swing tags. The web address to access the video is also included on the written materials. The design process involved developing an initial draft set of materials whose content and layout were informed using procedural task analysis; a review of human factors, instructional design literature and previous studies [15,16,17]; and a series of focus groups with users [25]. These were then refined through iterative user-testing ([name] et al., unpublished data) following the Sless and Wiseman model [19], which involved groups of the target population being exposed to the materials, with the subsequent refinement of the materials until a pre-defined criterion of a group average of 80% correct use and 80% correct comprehension was achieved.

The final prototype intervention materials target both the correct installation of the restraint within the vehicle and correct securing of the child within the restraint. An A3 instruction sheet and an online video detail the overall instructions and use process. The swings tags show what should be checked every trip and are designed to prompt users to check for the most common errors, checking the seat belt attachment (which anchors the child car seat to the car), the top tether strap attachment, and that the child is secured properly within the harness.

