### 2.2. Theoretical Framework for the Process Evaluation

As noted above, we believe the intervention materials will target the “skills and knowledge” component of the integrated model of behavior [22] and hypothesise that the intervention will increase the correct use of the restraint at six months post-purchase as depicted in the simple logic model illustrated in Figure 1.

The logic model depicted in Figure 1 will provide a framework for the process evaluation. As noted in Figure 1, we have assumed there are no physical constraints barring correct use among the study participants and that differences among study participants in their intention to correctly use the restraint can be assessed by measuring their confidence in and attitudes towards correct use. We therefore have defined confidence and attitudes to correct use as one of the external factors potentially impacting the relationship between the intervention and correct use. Other external factors being considered are level of prior experience using child car seats, access to other information about the correct use of car seats, the use of a professional restraint fitter, and the participants’ health literacy level.

Our hypothesised pathway between the intervention and the desired outcome requires the delivery of the intervention materials as planned (fidelity), that the participants receive each of the intended materials (dose delivered) and that participants access and use the materials (dose received). In the short term, we hypothesise that if the implementation of the intervention is successful, the participant will comprehend the intervention materials (which we have tested previously in a laboratory trial [18]) and recall key tasks about using a car seat correctly. This will lead the participant to continue to check key aspects of correct use, and ultimately, the car seat will continue to be correctly used six months after purchase.

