### 2.3. Process Measures

Table 1 summarises the planned process and outcome measures, data collection methods, and links to our evaluation framework depicted in Figure 1.

The reach of our intervention is fixed, with all participants expected to receive the same intervention components. The fidelity and dose delivered are also constant due to delivery of the materials with the purchased restraint and our processes for checking that the QR codes linking to online videos are continuing to work. As shown in Table 1, the bulk of the process evaluation measures are related to the dose received, and these will also be obtained through the semi-structured interview delivered at the six-month follow-up and researcher observation. Full details of the questions asked and construction of the dose received variables are provided in Supplementary Materials.

As detailed in Table 1 and Supplementary Materials, there are five measures for participation related to awareness and the self-reported use of the A3 instructions. An A3 instruction participation score will be calculated by summing the dichotomous codes (0 or 1) for each individual measure to deliver a score out of 5. For the swing tags, there are four individual measures, and for the video, there are three separate measures. The participation scores for each of these different components of participation will be calculated in the same way as described for the A3 instruction sheet.

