### 2.4. Outcomes

Proximal, medial and distal (primary) outcomes are summarised in the logic model shown in Figure 1, and the measures are summarised in Table 1. Our distal outcome is the same as the primary outcome being used and described above and is being objectively assessed by researchers during the six-month home visit inspection of the restraint. Our proximal and medial outcomes will be obtained through the survey with the parent at the same home visit. Further details of the questions used to elicit responses used to make these are assessments are provided in Supplementary Materials.

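### The swing-tag dose score contains a frequent-use item that overlaps with the continued-checking outcome, so the modelled path from tag dose to checking is partly built in

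*Protocol article*

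**What the plan says.** Section 2.2 sets out the pathway: dose received leads to comprehension and recall (proximal outcome), then to continued checking (medial outcome), then to correct use at six months (distal outcome). On the step after comprehension it says: "This will lead the participant to continue to check key aspects of correct use".

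Table 1 lists the components of swing-tag dose as "swing tag participation score (aware received swing tags, used swing tags, swing tags attached to restraint, swing tags used frequently". Section 2.3 gives the scoring rule for the A3 sheet, "An A3 instruction participation score will be calculated by summing the dichotomous codes (0 or 1) for each individual measure", and applies the same rule to the four tag items and the three video items. The three scores are kept separate.

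Section 2.1 describes what the tags are for: "The swings tags show what should be checked every trip and are designed to prompt users to check for the most common errors". Table 1 words the medial outcome as: "Did the participant continue to check key components of correct use".

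On timing and source, Section 2.3 says of the dose measures that "these will also be obtained through the semi-structured interview delivered at the six-month follow-up and researcher observation", and Section 2.4 says: "Our proximal and medial outcomes will be obtained through the survey with the parent at the same home visit". The distal outcome is inspected by a researcher (Sections 2.1 and 2.4). Section 2.5 plans a logistic regression of correct use and a structural equation model of the logic model through its intermediate outcomes. Section 2.6 expects 176 intervention participants with data.

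**The concern.** A dose variable placed at the start of a pathway should not contain the behaviour that the pathway is meant to explain. The tags exist to make the user check the restraint on each trip. A participant who reports using them frequently is, in large part, reporting that they kept checking. That answer is added into the exposure, and a near-equivalent answer from the same visit serves as a downstream outcome.

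The model would then tend to find a path from swing-tag dose to checking even if being aware of the tags, using them at all and attaching them made no difference. The evaluation includes the intervention arm only, so no randomised contrast can correct that path. The article's stated purpose is to learn how the intervention works. What is at stake is whether the swing tags are credited with a checking mechanism that partly reflects how the score was built.

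**Working it through.** **The plan's own figure.** Section 2.6 gives 220 per arm with 20% drop-out: 220 × 0.8 = 176. This reproduces and is the n used below.

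**Which items overlap.** There are 5 + 4 + 3 = 12 dose items.

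- A3 sheet: "aware received A3 instructions, read instructions, retained instructions, stored correctly, re-used instructions". These concern the leaflet, not checks of the restraint.
- Video: accessed, used, re-accessed. These concern the video, not checks of the restraint.
- Tags: awareness and attachment differ from checking, and use at any time is weaker than continued use. Only the frequent-use item is close to the medial outcome.

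So the overlap rests on one item of twelve, which is one of the four in the tag score.

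**Illustrative size.** The article gives no item frequencies, so all of these inputs are assumptions:

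- 90% are aware of the tags; 70% of those use them, so P(used) = 0.9 × 0.7 = 0.63; 80% of users attach them.
- 50% continue checking. Awareness, use and attachment are unrelated to checking.
- Among tag users, the frequent-use answer agrees with the checking answer with probability a.

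Let S be the four-item score and M the checking outcome.

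- Non-users who are aware (0.9 − 0.63 = 0.27) score 1. Users score on average 2 + 0.8 + 0.5 = 3.3, with variance 0.8 × 0.2 + 0.5 × 0.5 = 0.41.
- E(S) = 0.27 + 0.63 × 3.3 = 2.349.
- E(S²) = 0.27 + 0.63 × (3.3² + 0.41) = 7.389.
- Var(S) = 7.389 − 2.349² = 1.871, so SD(S) = 1.368. SD(M) = 0.5.
- Cov(S, M) comes only from the frequent-use item: 0.63 × (0.5a − 0.25).
- r = Cov / (1.368 × 0.5).
- Fisher z = atanh(r) × √173. The chance of p<0.05 is Φ(z − 1.96) + Φ(−z − 1.96).

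| a | Cov | r | z | Chance of p<0.05 |
|---|---|---|---|---|
| 0.5 (no overlap) | 0 | 0 | 0 | 5% |
| 0.7 | 0.063 | 0.09 | 1.22 | 23% |
| 0.8 | 0.0945 | 0.14 | 1.83 | 45% |
| 0.9 | 0.126 | 0.18 | 2.45 | 69% |

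Simulations with 4,000 replicates per setting agree: 22–23%, 45–46% and 67–70% for a = 0.7, 0.8 and 0.9.

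**Sensitivity to the assumptions.**

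- If only 30% of aware participants use the tags (P(used) = 0.27), the same formulas give 9%, 15% and 23%.
- In a different model, the frequent-use item copies the checking answer in a stated share of all participants, and checking prevalence is 30% to 70%. At 25% overlap r is 0.12–0.13 and the chance of p<0.05 is 37–40%. At 50% overlap r is 0.24–0.26 and the chance is 90–94%.

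**Without the frequent-use item.** The three-item score has a correlation of about zero with checking in every setting, and the rate of p<0.05 returns to about 5%.

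**The case against.** **Frequency of use is legitimate dose.** The tags are meant for every trip, and Section 2.2 defines dose received as accessing and using the materials. A score without frequency rates a one-time user the same as a daily user. Frequent tag use may also truly cause checking, which is the hypothesis; the illustration assumes that it does not and does not show it. This stands. It is a reason to keep the item in the analysis as its own variable. It does not cure the problem that, inside the summed score, a causal effect and a repeated report of one behaviour cannot be told apart.

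**The wording is unseen.** The exact questions are in the supplementary material and the paths are in Figure 1; neither is shown. This stands for the size of the overlap. It does not change the item's place in the score, which Table 1 and Section 2.3 fix.

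**The limitation is partly disclosed, and dose is not all self-report.** Section 3 acknowledges social desirability bias in self-reported measures, but not shared content. Section 2.3 mentions researcher observation as a further source of the dose measures, so a common reporter is not established for every item. Table 1 nevertheless lists survey questions as the method for dose received.

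**Stronger readings.** A reader might infer that all three participation scores are contaminated, or that adherence cannot be separated from outcome at all. The documents do not support either. Returning to a leaflet or video is not checking the restraint, and those scores are calculated separately. A reader might also suppose that people re-use the sheet or video because they are in difficulty, which would bias those scores the other way; nothing in the article documents this. The items are coded individually, so separation is possible. The logistic regression uses a researcher-inspected outcome that shares no item with the dose scores.

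**Conclusion.** The point holds for one path. As the score is defined, the association between swing-tag dose and continued checking is partly built in by one of the four tag items. The direction is clear from Table 1 and Sections 2.1 to 2.3. The size is not known. Under the main illustration, about 23% to 70% of studies with 176 participants would reach p<0.05 when the other three items have no relation to checking; with low tag use it is about 9% to 24%. Both ranges rest on assumed prevalences and on 70% to 90% agreement between the two answers.

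The A3 score, the video score and the logistic regression on correct use are outside this finding. It is a modest, inexpensive improvement to what can be concluded about the swing-tag mechanism, not a flaw in the trial's primary comparison.

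**What to change.** Amend Section 2.3 and Table 1 for the dose-to-checking path only:

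1. Score swing-tag dose from the awareness, use and attachment items (0 to 3).
2. Treat frequent tag use as a separate sustained-use variable, placed at the medial step beside continued checking.
3. Also report the path with the full four-item score.
4. State in advance that the swing tags will be credited with a checking mechanism only if the path holds without the overlapping item.

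The A3 and video scores and the logistic regression need no change on this account.

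The cost is re-scoring of items already collected, one extra analysis, and a slightly narrower score that no longer separates one-time from frequent tag users. That distinction is kept in the separate variable.

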## 2. Materials and Methods

In our randomised controlled trial, we aim to recruit 440 people who have decided to purchase one of two different commercially available child restraints. The restraints include a rearward/forward facing convertible car seat (suitable for children aged 0 to approximately 4 years) and a convertible forward facing/booster seat restraint (suitable for children from 4 years to approximately 8 years). Both are designed to be installed in a vehicle using the vehicle seatbelt and a top tether. Neither includes the means for attachment to ISOFIX connectors in a vehicle. The rationale for not including ISOFIX-compatible restraints is that while the mandatory Australian product standard (AS/NZS 1754) allows for ISOFIX-compatible restraints, it requires that all child restraint systems (including those that are ISOFIX compatible) are able to be anchored to the vehicle by the seat belt and top tether anchorage system. This, together with the fact that the uptake of ISOFIX-compatible restraints is still relatively low, means the seatbelt/top tether anchorage system is currently the dominant anchorage system in Australia. The specific makes and model of restraints used in this study were arbitrarily chosen during the intervention material design process. The recruitment strategies encompass a broad-brush approach to reaching people who may soon be purchasing a new child restraint. These strategies include posters and postcards in the ante-natal areas of hospitals, child care centres and pre-schools; the use of social media such as parenting forums and Facebook groups; and the websites of organisations that may be visited by parents and expectant parents. On recruitment, participants are randomly allocated to the control group (*n* = 220) or the intervention group (*n* = 220), and control or intervention materials are delivered to the participants with the purchased restraint along with the usual materials supplied with the restraint. The study materials are therefore supplementary to the usual packaging, instructions and labels supplied with the restraint, as required by the mandatory Australian product standard (AS/NZS 1754). The intervention group receive the set of materials we developed using the consumer-driven design process and previously shown to be effective in a laboratory trial [18]. The materials delivered to the control group consist of a generic child passenger safety postcard describing the legal requirements for child restraint use in New South Wales, Australia. Participants are reimbursed AU$100 for their involvement in the study. As we aim to examine the impact of implementation and mechanisms underpinning the effect of the intervention, this process evaluation will only include data collected from participants within the intervention group of our pragmatic field trial. The process evaluation will be undertaken blinded to trial outcomes as recommended by MRC guidelines [23].

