Prior to being sent their child restraint, participants are told over the phone that the study materials will be inside the box in which the child restraint is packaged. They are instructed to look out for the zip-lock bag with the study materials inside. To keep participants “blinded” to their group allocation, they are informed that there are two sets of information materials, that each is technically correct and approved by child safety experts, and that participants will be randomly assigned to one or the other. The intervention materials come with a printed set of instructions recommending that the A3 instruction sheet be kept, folded, in the pouch on the child car seat provided for the manufacturer’s instruction booklet and that the swing tags be adhered to the plastic shell of the car seat, towards its rear, using the adhesive attachment provided. As part of the participant information statement, participants are told that they do not need to do anything differently than they are inclined to do, in terms of the installation of and use of the child restraint and the use of any informational materials about child restraints.

Once a participant is enrolled in the study (i.e., has purchased the car seat), they are assigned the next-in-line participant identification number, which has a pre-assigned random group allocation: intervention or control. A researcher gathers the relevant study materials and checks, using a QR code reader, that the QR code link is working properly on every third set of intervention group materials. The study materials are then placed in a transparent zip-lock bag. The zip-lock bag is inserted into the top of the box of the purchased car seat, through the open slit of the cardboard flaps. The box does not need to be opened to do this. The address label for the courier is then taped to the box, and the courier is contacted for the pick-up of the car seat and delivery to the participant.

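### Restraint type is missing from the stated set of external factors, so it may confound the within-arm associations of prior experience and dose with misuse

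*Protocol article*

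**What the plan says.** Section 2 (Materials and Methods) enrols "people who have decided to purchase one of two different commercially available child restraints". One is "a rearward/forward facing convertible car seat (suitable for children aged 0 to approximately 4 years"; the other is "a convertible forward facing/booster seat restraint (suitable for children from 4 years to approximately 8 years". The buyer chooses the seat; only the study materials are randomised. On installation the seats are alike: "Both are designed to be installed in a vehicle using the vehicle seatbelt and a top tether". The same section restricts the process evaluation to intervention-group data.

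Section 2.5 (Analysis) plans a logistic regression for correct use that takes account of intervention delivery and external factors, followed by structural equation modelling (SEM) of the logic model. The external factors are named twice. Section 2.2 puts confidence and attitudes first and continues "Other external factors being considered are level of prior experience using child car seats", then adds other information, use of a fitter and health literacy. Table 1 gives the same five: "Health literacy level, prior experience with car seats, access to correct use information from other sources, use of a restraint fitter, confidence/attitude". Neither list contains restraint type or child age, and no section mentions analysing, adjusting or stratifying by restraint type.

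The trial should know the type for every participant. Under section 2.1, "The zip-lock bag is inserted into the top of the box of the purchased car seat" by study staff, and a researcher inspects the restraint at the six-month visit.

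**The concern.** With one arm only, randomisation does not balance high-dose against low-dose users, or experienced against inexperienced ones. A variable related both to the factor and to misuse biases the association unless it is in the model.

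Restraint type is a credible variable of this kind:

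- **Experience.** Section 2.3 gauges it partly by asking about other children. Section 2 recruits from ante-natal areas as well as child care centres and pre-schools. A seat for 0–4 years and one for 4–8 years could well attract buyers with different histories.
- **Misuse.** Section 2.1 counts one serious error, or two or more minor ones. Seats with different modes may offer different numbers of possible errors.
- **Dose.** The tags prompt checks of seat belt, tether and harness. How useful these prompts are, and how often the sheet is re-used, may vary by seat.

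The stated purpose is to learn which external factors alter the effect of the materials and to guide implementation. Crediting a seat difference to experience, or to use of the sheet, tags or video, would misdirect that.

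**Working it through.** **The plan's own figure.** 220 × (1 − 0.20) = 176 intervention participants, as section 2.6 states. The sample size is not at fault here.

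**Inputs.** The documents give no seat split, no misuse rate by seat, and no link of seat to experience or dose. All of the following are assumptions:

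- share buying the older-child seat (B): 10% to 50%;
- prevalence of the factor (experience, or high dose) in seat A and seat B: 50%/70%, 40%/80% or 30%/90%;
- outcome risk 50% in seat A, with a seat-to-outcome odds ratio (OR) of 1.5, 2 or 3;
- true OR of the factor: 1.

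**Formula.** With q the share of seat B, e₀ and e₁ the factor prevalence in A and B, and r₀ and r₁ the outcome risk in A and B, the crude risks are

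- factor present: [(1−q)e₀r₀ + q e₁r₁] / [(1−q)e₀ + q e₁];
- factor absent: [(1−q)(1−e₀)r₀ + q(1−e₁)r₁] / [(1−q)(1−e₀) + q(1−e₁)].

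The crude OR is the ratio of the two odds.

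**Worked case:** q = 0.30, prevalence 40%/80%, seat OR 2 (r₀ = 0.500, r₁ = 0.667).

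- Present: (0.28 × 0.500 + 0.24 × 0.667) / 0.52 = 0.30 / 0.52 = 0.577.
- Absent: (0.42 × 0.500 + 0.06 × 0.667) / 0.48 = 0.25 / 0.48 = 0.521.
- OR = (0.577/0.423) / (0.521/0.479) = 1.25, although the true value is 1.

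**Range.** The lowest non-null case (10%, 50/70, seat OR 1.5) gives 1.03. The highest (50%, 30/90, seat OR 3) gives 1.94. If seat type is unrelated to the factor or to the outcome, the crude OR is exactly 1.00. Reversing the seat effect gives ORs below 1. For example, with equal numbers, misuse 50% in A and 30% in B, and experience 40% and 90%:

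- experienced: (0.4 × 0.5 + 0.9 × 0.3) / 1.3 = 36.2%;
- inexperienced: (0.6 × 0.5 + 0.1 × 0.3) / 0.7 = 47.1%;
- OR 0.635.

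**Type I error at n = 176.** This comes from logistic regression on one binary null factor, 2,000 simulated data sets per row, nominal 5%:

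| Share of B | Prevalence A/B | Seat OR | Crude OR | Without seat type | With seat type |
|---|---|---|---|---|---|
| 30% | 50/70 | 1.5 | 1.07 | 5.7% | 5.3% |
| 30% | 40/80 | 2 | 1.25 | 11.5% | 5.0% |
| 50% | 40/80 | 2 | 1.33 | 14.5% | 5.5% |
| 50% | 30/90 | 3 | 1.94 | 54% | 5.1% |

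The simulation error near 5% is √(0.05 × 0.95 / 2000) ≈ 0.5 points, so the first row shows no clear difference.

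**Cost of the covariate.** Assume 35% misuse in the arm (the introduction's one-in-two error rate, less the 15-point target). Then 176 × 0.35 ≈ 62 events. Three dose scores and five external factors at one parameter each make eight: 61.6 / 8 = 7.7 events per parameter, and 61.6 / 9 = 6.8 with seat type added.

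**The case against.** The strongest reply is that this rests on an absence in a condensed article. Table 1 lists process measures collected mainly by survey, and restraint type is a design variable known at purchase, so it would not naturally appear there. Section 2.5 describes the model in one sentence and excludes nothing. Figure 1, the Supplementary Materials and any analysis plan are not shown. This stands in part: a reader might infer that the seats will certainly be pooled unadjusted, and the documents do not prove that. But the article does not leave covariates open. It names the external factors twice, section 2.3 says that Figure 1 defines the set, and section 2.5 ties the model to it. A stated set that lacks the variable is more than missing detail.

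A reader might also infer that experience, dose and outcome are in fact confounded by seat. The documents do not support this: nothing in them links seat to any of the three. Nor are the seats different in every respect, as they share the same anchorage.

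The causal order for experience deserves care. Experience comes before purchase and may help determine which seat is bought, so seat type may lie partly on the path from experience to misuse. Adjustment then changes the meaning of that coefficient as well as removing bias. For dose the difficulty does not arise, since the seat is chosen before the materials arrive.

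Two extensions are tempting and should not be added. The mode in use at the visit is observed six months after exposure and may be affected by the materials, so conditioning on it could introduce bias. A test of arm by seat type lies outside an intervention-arm evaluation, and the trial is sized for a 15-point main effect, not an interaction.

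**Conclusion.** The point holds as a possible bias, not a demonstrated one. The plan states an adjustment set for observational, within-arm associations, and that set omits a pre-exposure variable that the trial should already hold. Whether this matters depends on the seat split and on how seat type relates to experience, dose and misuse, none of which the documents give. The bias could be nil; in the stronger assumed scenarios it is large enough to produce false findings well above the nominal 5%. A reader might extend this to the main trial result, but allocation to materials is random, so the comparison between arms is not confounded by restraint type. The change is worth making because it is cheap and because the plan as published cannot rule the bias out.

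**What to change.** Add the restraint type purchased to the stated covariates in sections 2.2 and 2.5 and in Table 1. Include it in the logistic model and in the outcome equations of the SEM, or give the reason for leaving it out. Report the three dose scores and serious misuse descriptively by restraint type.

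No new data collection should be needed. The cost is about one parameter per equation, which at the assumed 35% misuse takes the logistic model from roughly 7.7 to 6.8 events per parameter. The write-up should say that the experience coefficient is then conditional on seat type.
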